### **18.2.3 Tenderness**

The parent/legal guardian will be asked to assess and record in the diary card whether tenderness is present at the injection site and grade it on the following scale:

|   |                                                                |
|---|----------------------------------------------------------------|
| 0 | Absent                                                         |
| 1 | Tenderness present, does not interfere with routine activities |

- |   |                                                                              |
|---|------------------------------------------------------------------------------|
| 2 | Tenderness present, cries or shows discomfort while doing routine activities |
| 3 | Tenderness interfering with limb movement                                    |

### **18.3 General Reactions**

#### **18.3.1 Temperature**

Axillary temperature will be measured by the parent/legal guardian and recorded from the vaccination day (day 0) to day 4 post-vaccination. A digital thermometer will be provided by the study team on Visit 1. Temperature will be considered as fever if >38.0 centigrades. In the event of fever, temperature will be collected daily until its resolution.

### **18.4 Unsolicited Reactions**

These are any adverse events that are not pre-listed in the diary card but may be reported on the diary card by the participant or through interview with the participant. These will be reported in the CRF/source document adverse event form.

AEs considered related to the study medication by the investigator or the sponsor will be followed until resolution or the event is considered stable.

The following attributes must be assigned by the investigator to all adverse events occurring within 4 days of pneumococcal immunisation and all medically significant adverse events occurring during the study: description, date of onset and resolution date, severity, assessment of relatedness to study medication, other suspected drug or device and action taken.

The investigator may be asked to provide follow-up information.

All related AEs that result in a participant's withdrawal from the study or are present at the end of the study, should be followed up until a satisfactory resolution occurs.

All deaths occurring during the study must be reported to the Sponsor/CI. These include deaths within 30 days of the final dose of study medication and deaths up to the last formal follow-up observational period, whichever is longer. For all deaths, available autopsy reports and relevant medical reports will be made available for reporting to the relevant authorities.

It will be left to the investigator's clinical judgment whether or not an AE is of sufficient severity to require the participant's removal from treatment. A participant may also voluntarily withdraw from treatment due to what he or she perceives as an intolerable AE. If either of these occurs, the patient must undergo an end of study assessment and be given appropriate care under medical supervision until symptoms cease or the condition becomes stable. The severity of events will be assessed on the following scale: 1 = mild, 2 = moderate, 3 = severe. The relationship of AEs to the study medication will be assessed.

### **18.5 Other reportable information**

The following events will also be reported to Pfizer:

- Report of pregnancy exposure to a Pfizer product (information about use in pregnancy encompasses the entire course of pregnancy and delivery, perinatal and neonatal outcomes, even if there were no abnormal findings)
- Report of lactation exposure to a Pfizer product
- Overdose
- Spontaneous reports of an unexpected therapeutic or clinical benefit associated with the use of a Pfizer product
- Abuse (for example, use for non-clinical reasons)
- Inadvertent or accidental exposure
- SIDS
- Apnoea
- Autism
- Hypotonic hyporesponsive episode (HHE)

- Metal poisoning
- Lack of effect

## **19. STATISTICS AND ANALYSIS**

### **19.1 Number of Participants**

Of the 286 children randomised in the original study, approximately 240 were enrolled in the sites that will be participating in this follow on study. Of these, approximately 200 completed the study. It is anticipated that 50% of these participants are likely to take part in this follow-on study, therefore the study population is likely to be approximately 100 children. It is expected that approximately 50% of these will have received PCV13 and the other 50% PCV7.

### **19.2 Description of statistical methods**

Two sided binomial exact confidence intervals will be constructed around the proportion of subjects achieving specified antibody concentrations, and around rates of local and systemic reactions.

The antibody concentrations will be logarithmically transformed for analysis, since the untransformed values are highly skewed. For each serotype separately, and at each time point, geometric means of the antibody concentrations from each of the blood draws will be calculated. Two-sided, 95% confidence intervals will be constructed by back transformation of the confidence intervals for the mean of the logarithmically transformed assay results computed using the Student t distribution.

In addition, the geometric mean fold-rise for the serotype-specific concentrations will be derived from the exponent of the difference between the logarithmically transformed assay results before and after the booster dose. The corresponding 95% confidence intervals will be computed using the same method mentioned above, i.e. the confidence interval will be obtained on the log transformed scale, and then back transformed to give the result on the original scale.

A Chi-square test or Fisher's exact test will be used to compare the proportions between groups of participants.

Two-sample t-test will be used to compare the logarithmically transformed concentrations between the groups, or else analysis of variance, to adjust for baseline values, as appropriate. Differences between the two groups and the corresponding 95% confidence intervals will be calculated. Comparisons between the two groups will be carried out based on the allocated groups.

A full statistical analysis plan will be prepared by the study statistician prior to the analysis.

### **19.3 Level of statistical significance**

We shall take  $p < 0.05$  to denote statistical significance, as this is the standard convention.

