Conjugation of the pneumococcal PS to a protein converts the PS to a T-cell dependent antigen, allowing infants to mount an effective immune response. Using this technology, a 7-valent pneumococcal conjugate vaccine (PCV7) was developed by Wyeth vaccines (now Pfizer). PCV7 contains PS from serotypes 4, 6B, 9V, 14, 18C, 19F and 23F, the pneumococcal serotypes responsible for the majority of IPD in industrialised countries, conjugated to non-toxic diphtheria toxin cross-reacting material (CRM197). Controlled clinical trials with PCV7 show that it is effective in preventing IPD and pneumonia due to serotypes in the vaccine.

Since licensure of PCV7 in the United States in 2000, its effectiveness in preventing IPD in infants has been definitively documented. Data from the Active Bacterial Core Surveillance (ABC) network show that in 2001, the incidence of IPD in children less than 5 years of age had declined by 56%, and in 2004 by 76%, with a 96% decline in IPD caused by vaccine serotypes. In addition to this direct effect of the vaccine, vaccination of children has also reduced the incidence of disease in adults. There were statistically significant declines in IPD in adults 20 years and older after the introduction of PCV7, the largest in those greater than 65 years. The absolute number of cases prevented by this indirect effect of PCV7 is actually estimated to be larger than the direct effect, which makes universal vaccination highly cost effective.

The ABC data have also shown small, but statistically significant increases in pneumococcal disease due to non-vaccine serotypes in both infants and adults. Serotypes 19A, 3, 15, 22F, 33F, and 35 have all been isolated, with 19A being the most prevalent. Genetic typing of serotype 19A strains identified the presence of the primary clone seen before the introduction of PCV7, as well as new genetic types previously associated with other, principally vaccine serotypes; this appears to be the result of capsular switching.

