### **5.2 Secondary Objectives**

To assess the proportion of participants, immunised with the 7-valent pneumococcal conjugate vaccine (PCV7) at 2, 4 and 12 months of age, who have IgG concentrations  $\geq 0.35\text{mcg/ml}$  for PCV13 serotypes at the time when preschool booster vaccinations are due (at 40 months\* of age) and comparing these to the

proportion of participants achieving this threshold after infant immunisation with PCV 13.

To assess and compare PCV13 serotype-specific IgG geometric mean concentrations (GMCs), opsonophagocytic activity (OPA) geometric mean titres (GMTs) and the proportion of participants with PCV13 serotype-specific OPA titres  $\geq$  1:8 at 40 months\* of age in children immunised in infancy with either PCV7 or PCV13.

To assess and compare PCV serotype-specific IgG GMCs, OPA GMTs and the proportion of participants with IgG concentrations  $\geq$  0.35mcg/ml and OPA titres  $\geq$  1:8 one month following a booster dose of PCV13 at 40 months\* of age in children previously immunised with PCV7 and PCV13 at 2, 4 and 12 months of age.

To determine reactogenicity of the pre-school PCV13 booster in terms of rates of local and systemic reactions following vaccination.

To investigate the influence of genetic polymorphisms on the above immunological markers following infant immunisation with PCV7 or PCV13 and following a booster dose of PCV13 at 40 months\* of age and on the nature of adverse reactions observed after this booster immunisation.

To measure the pneumococcal serotype-specific memory B cells frequencies before and 1 month after a dose of PCV13 at 40 months\* of age in a subset of children previously immunised with PCV7 or PCV13 at 2, 4 and 12 months of age (serotype studies to include serotypes including 4, 14, 23F (present in PCV7) and, 1, 3, 19A).

\* Ages are approximate

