## **10. TREATMENT OF TRIAL PARTICIPANTS**

### **10.1 Interventions:**

#### Study vaccine

##### **10.1.1 13-valent Pneumococcal Conjugate Vaccine**

PCV13 contains saccharides from pneumococcal serotypes 1, 3, 4, 5, 6A, 6B, 7F, 9V, 14, 18C, 19A, 19F, and 23F individually conjugated to cross-reacting material (CRM197). The vaccine is formulated to contain 2.2 pg of each saccharide, except for 4.4 pg of 6B, with a total nominal dose of 29 pg CRM197 per 0.5-mL dose. The final formulation contains 5 mM succinate buffer, with 0.125 mg of aluminum as aluminum phosphate per 0.5-mL dose. The vaccine is administered intramuscularly by injecting 0.5 mL into the non dominant deltoid muscle at Visit 1.

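### Section 19.3 makes unadjusted p<0.05 the mark of significance for up to 104 secondary PCV7-versus-PCV13 comparisons; these p-values should be labelled descriptive

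*Protocol*

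**What the plan says.** Section 19.3 is one sentence. It takes p<0.05 "to denote statistical significance, as this is the standard convention", with no restriction to particular endpoints or analyses.

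Section 5.2 sets the comparisons:

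- At 40 months, the share of PCV7-primed children at or above 0.35 mcg/ml is to be set against the "proportion of participants achieving this threshold after infant immunisation with PCV 13".
- Also at 40 months, the aim is "To assess and compare PCV13 serotype-specific IgG geometric mean concentrations (GMCs), opsonophagocytic activity (OPA) geometric mean titres (GMTs"), together with the proportion with OPA of at least 1:8.
- One month after the booster, all four measures are to be assessed and compared "in children previously immunised with PCV7 and PCV13 at 2, 4 and 12 months of age".

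Section 19.2 supplies the tests. Chi-square or Fisher's exact test "will be used to compare the proportions between groups of participants", and log concentrations are compared by a two-sample t-test or by an analysis of variance adjusting for baseline. The same section, and section 19.4 for the 0.35 threshold, also plan group differences with 95% confidence intervals.

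Section 19.4 estimates the primary endpoint as a proportion per serotype with an exact binomial interval. It calls the reactogenicity and B-cell summaries descriptive but gives no such label to the comparisons by priming vaccine. Section 19.2 promises a full SAP before the analysis; it is not at hand.

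**The concern.** A single unqualified threshold, applied to many parallel serotype comparisons, produces some results below it by chance. The protocol states no order, family or adjustment for them, does not call them exploratory, and has no primary test before them.

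The seven serotypes common to both vaccines are the sensitive part, because little or no effect of the priming vaccine is plausible there. Under section 19.3 an isolated p<0.05 on one of them would be reported as statistically significant and could be read as PCV13 priming being better or worse for a PCV7 serotype. The background section says the study is meant to fill a gap in the immunogenicity data relevant to a pre-school booster, so such a reading could carry weight.

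**Working it through.** **Inputs from the protocol**

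- 13 serotypes (section 10.1.1): "PCV13 contains saccharides from pneumococcal serotypes 1, 3, 4, 5, 6A, 6B, 7F, 9V, 14, 18C, 19A, 19F, and 23F".
- 7 of them shared by both vaccines (section 4): "PCV7 contains PS from serotypes 4, 6B, 9V, 14, 18C, 19F and 23F".
- 4 measures: IgG at or above 0.35 mcg/ml, IgG GMC, OPA GMT, OPA at or above 1:8 (section 5.2).
- 2 time points: before the booster and one month after it.
- Threshold 0.05. The sidedness of the tests is not stated; the intervals are ("Two-sided, 95% confidence intervals will be constructed by back transformation"), so two-sided tests are assumed.
- Sample size (section 19.1): 200 completers × 0.5 = 100, about 50 per group. This reproduces the protocol's figure. It rests on feasibility, and there is no power statement to check.

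**Number of comparisons**

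- All: 13 × 4 × 2 = 104. IgG measures only: 13 × 2 × 2 = 52.
- Shared serotypes: 7 × 4 × 2 = 56. IgG measures only: 7 × 2 × 2 = 28.

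The per-protocol repeats and the tests of genetic polymorphisms are not counted.

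**Expected chance results on the shared serotypes, if priming makes no difference there**

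At the nominal size of every test: 56 × 0.05 = 2.8.

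Of the 56, 28 compare means and 28 compare proportions. The comparisons of means keep their 5% size: 28 × 0.05 = 1.4. Fisher's test is conservative at 50 versus 50, so its exact size depends on the true proportion:

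| True proportion | Fisher size | Expected number among 56 |
|---|---|---|
| 50% | 3.52% | 1.4 + 28 × 0.0352 = 2.39 |
| 80% | 2.82% | 1.4 + 28 × 0.0282 = 2.19 |
| 95% | 0.72% | 1.4 + 28 × 0.0072 = 1.60 |
| 99% | about 0% | 1.40 |

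The uncorrected chi-square test stays near its nominal size in mid-range (5.69% at a true proportion of 50%, giving 1.4 + 28 × 0.0569 = 2.99) and drops close to 100% (0.19% at 99%, giving 1.45). A working range is therefore about 1.4 to 2.8.

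For the 28 IgG comparisons alone, the nominal figure is 28 × 0.05 = 1.4. With Fisher for the 14 proportions it is 14 × 0.05 = 0.7 at the lowest and 0.7 + 14 × 0.0352 = 1.19 at a true proportion of 50%.

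**Chance of at least one**

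If all 56 tests were independent and of exact size: 1 − 0.95^56 = 0.94. They are not independent. In simulations with assumed correlations between serotypes (0 to 0.7), measures (0 to 0.9) and visits (0 to 0.7), the chance ran from 0.94 with no correlation to 0.45 with the strongest. Correlation does not change the expected number.

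**The case against.** **It can be left to the SAP.** Families, ordering and exploratory labels commonly belong there, and a SAP that applied an adjustment at the 0.05 level could be seen as compatible with section 19.3. This stands as far as a missing adjustment scheme is not itself a fault of the protocol. It does not remove the point, because section 19.3 is a stated rule: followed exactly, it calls any single p<0.05 significant.

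**No confirmatory claim is at risk.** The primary objective is estimation and the sample size is set by feasibility. This stands and limits the point to secondary comparisons. The lack of a primary test is a feature of an estimation study, not a defect.

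**The intervals are already planned.** They are. Only the use of the word significant is at issue.

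**The count may be too high.** Section 19.4 spells out a comparison by priming vaccine only for IgG at or above 0.35 mcg/ml; the OPA comparisons rest on section 5.2. Hence up to 104, with 52 as the IgG-only count. The per-protocol repeats concern a subset of the same children and are not a fresh set of chances.

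**A stronger reading is tempting.** A reader might infer that false differences on the shared serotypes are certain to be declared. The protocol does not support that. It never says the two priming groups are alike on those serotypes, and any true difference there would not be a false positive. The 1.4 to 2.8 is an expectation under an assumed null, and the chance of at least one depends on correlations the protocol does not give.

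A reader might also conclude that a formal adjustment must be imposed. That is a debatable trade-off. With 50 per group, a difference of about 0.566 SD has 80% power at 0.05. At Holm's first step this falls to about 53% for a family of seven (0.05/7) and 56% for a family of six (0.05/6), although later steps cost less. Adjusting within each measure and visit would still leave 4 × 2 = 8 shared-serotype families at 5% each: 1 − 0.95^8 = 0.34 for at least one false claim if independent.

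**Conclusion.** The point holds as a wording defect with limited reach. Section 19.3 attaches the label of statistical significance to any p<0.05, while section 5.2 generates up to 104 secondary comparisons (52 for IgG alone). On the 56 shared-serotype tests, about 1.4 to 2.8 chance results below 0.05 are expected.

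That size rests on four assumptions: no true difference on the seven shared serotypes, two-sided tests, about 50 children per group, and all the comparisons in section 5.2 being tested. The primary single-group estimates are untouched. The SAP may already handle the matter, but section 19.3 as written does not point to it.

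**What to change.** Reword section 19.3 to say three things:

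1. The secondary serotype-by-serotype comparisons by priming vaccine are interpreted from the group differences or ratios with 95% confidence intervals already planned in sections 19.2 and 19.4.
2. Unadjusted p-values for these comparisons are descriptive and are not used to declare significance for individual serotypes.
3. Any claim of significance among them requires a multiplicity adjustment pre-specified in the SAP.

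No particular adjustment need be fixed in the protocol. The cost is a change of wording, with no new data or analyses. The downside is that an isolated serotype difference can no longer be called significant on an unadjusted p-value, even where it is real.

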### **19.4 Analysis and endpoints**

For the primary objective (persistence of antibody to 40 months) the analysis population will consist of all participants who provide a blood sample at visit 1 (intention to treat population for antibody persistence),

For the response to PCV13 immunogenicity analyses, the analysis population will consist of all participants receiving a dose of PCV13 and providing a blood sample at visit 2 (intention to treat population for booster dose response).

For analysis of reactogenicity, the analysis population will be defined as all those receiving a dose of PCV13 and providing any reactogenicity or safety data (intention to treat analysis for reactogenicity).

For each of the above analyses, a per-protocol population analysis (excluding those meeting the criteria defined in points 2 a, b or c in section 8.2) will be performed.

For each of the pneumococcal serotypes included in the PCV13 the proportion of subjects achieving an IgG antibody concentration  $\geq 0.35$  mcg/mL at 40 months of age after the infant series will be computed along with a 2-sided 95% confidence interval for the proportion using the Binomial exact method.

For each serotype of pneumococcal IgG separately, geometric means of the antibody concentrations from each of the blood draws will be calculated, along with their 95% confidence intervals. Similar procedures will be used to evaluate the pre- and post 40 month booster dose assay data. In addition, the geometric mean fold-rise for the serotype-specific pneumococcal IgG concentrations will be derived from the exponent of the difference between the logarithmically transformed assay results before and after the booster dose, with corresponding 95% confidence intervals.

The proportion of participants with antibody concentrations  $\geq 0.35$  mcg/mL between those primed with PCV7 and PCV13 will be compared. Differences between the two groups and the corresponding 95% confidence intervals will be calculated.

The rates of reactogenicity of the pre-school PCV13 booster (in terms of rates of each separate local and systemic reactions following vaccination) will be presented along with their 95% confidence intervals.

Reactogenicity data will be summarised descriptively and the association between any genetic polymorphism and outcomes of booster doses will be assessed using Fisher's exact test.

B cell response data will be summarised descriptively.

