The duration of serotype-specific antibody persistence following primary immunisation with PCV13 is not known. Further, there are no data on the serotype-specific IgG persistence to 40 months following a 2, 4 and 12 month schedule with PCV7. Although the largest burden of pneumococcal disease is in the under 2 year olds, there is also a significant burden of invasive pneumococcal disease in the 2 to 5 year old age group. This age group is also important for the carriage and spread of pneumococcus; hence, pneumococcal serotype-specific immunity of this age-group is likely to be important in reducing disease burden and enhancing herd immunity. It would therefore be important to ensure that serotype-specific antibodies persist following a primary vaccination program, and if not, to assess the immune response to a pre-school booster of pneumococcal vaccine.

PCV13 has recently replaced PCV7 in the UK immunisation schedule and an ongoing enhanced surveillance program will monitor the impact of this change on the incidence of the additional 6 serotypes contained in PCV13. One option to further enhance the control of these serotypes is the administration of a pre-school booster dose of PCV13 to those children immunised in infancy with PCV7, however, at present there are no immunogenicity data to inform such an option.

An important functional measure of protective immunity induced by pneumococcal vaccines appears to be the assay for opsonic capacity, which is the host's primary mechanism of protecting itself against pneumococcal infections; pneumococcal vaccines are designed to induce opsonic antibodies. We will therefore use a standardised opsonophagocytosis assay OPA methodology to evaluate the protective immunity induced by the PCV7 and PCV13 schedules employed in these studies in addition to measuring serotype specific IgG concentrations.

We have previously found that the B cell response to conjugate vaccines generates memory cells which, in infants, predict both the persistence of antibody and the response to booster doses of vaccines. There is some variation in the responses to different serotypes in PCV13 and we have developed B cell assays that can be used to explore the quantity and phenotype of these responses. We will use these assays to describe the B cell response to a booster dose of PCV13.

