### *Secondary Endpoint*

The proportion of participants with PCV13 serotype-specific IgG concentrations  $\geq 0.35\text{mcg/ml}$  at 40 months\* of age following immunisation with PCV7 at 2, 4 and 12 months of age.

The PCV13 serotype-specific IgG GMCs, OPA GMTs and proportion of participants with OPA titres  $\geq$  at 40 months\* of age in children primed with either PCV7 or PCV13.

The PCV13 serotype-specific IgG GMCs, OPA GMTs and proportion of participants with IgG concentrations  $\geq 0.35\text{mcg/ml}$  and OPA titres  $\geq 1:8$ , 1 month following a dose of PCV13 at 40 months\* of age in children who have received PCV7 or PCV13 at 2, 4 and 12 months of age.

Rates of local and systemic reactions (reactogenicity) following vaccination with the pre-school PCV13 booster at 40 months\*.

The identification of genetic polymorphisms influencing the above immunological markers and adverse reactions to vaccines.

The frequency of PCV13 specific memory B cells in a subset of participants before and after immunisation at 40 months\* of age as determined by B cell ELISPOT and where sufficient B cells are available for analysis, phenotyping of these cells.

\* Ages are approximate.

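### The reactogenicity population in Section 19.4 admits children without diary data, and reaction rates are not specified by priming group

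*Protocol*

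**What the plan says.** Section 19.4 of the protocol sets three analysis populations. The persistence set requires a blood sample at visit 1. The booster-response set requires a PCV13 dose and a blood sample at visit 2. The reactogenicity set is "all those receiving a dose of PCV13 and providing any reactogenicity or safety data".

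For the analysis itself, Section 19.4 states: "The rates of reactogenicity of the pre-school PCV13 booster (in terms of rates of each separate local and systemic reactions following vaccination) will be presented", with 95% confidence intervals, and adds that these data are summarised descriptively. Section 19.2 specifies exact binomial intervals for them. The objective in Section 5.2 is "To determine reactogenicity of the pre-school PCV13 booster in terms of rates of local and systemic reactions following vaccination", and the endpoint in Section 6.2 is "Rates of local and systemic reactions (reactogenicity) following vaccination with the pre-school PCV13 booster at 40 months". None of these mentions the vaccine used for priming.

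The antibody items do. For the IgG threshold, Section 19.4 says that the proportions "between those primed with PCV7 and PCV13 will be compared", with differences and 95% confidence intervals. Section 19.2 also gives a general rule: "A Chi-square test or Fisher's exact test will be used to compare the proportions between groups of participants".

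**The concern.** There are two weaknesses, both in text that the protocol states.

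**Denominator.** Each immunogenicity set requires the sample from which its endpoint is measured. The reactogenicity set does not require the diary, which is the stated source for redness, swelling, tenderness and temperature (Sections 18.2 to 18.3.1). Any safety information is enough for entry. If the set is then used as the denominator, children in whom no solicited reaction could have been recorded enlarge n without being able to contribute an event. The error can go only downwards, which is the favourable direction for a tolerability endpoint.

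**Priming group.** For children primed with PCV13 at 2, 4 and 12 months, the study dose is a fourth dose of PCV13. For PCV7-primed children it is the first dose of the six additional conjugates. Section 4 names "administration of a pre-school booster dose of PCV13 to those children immunised in infancy with PCV7" as an option for further control of those serotypes. If only an overall rate were reported and the groups differed, that rate would not describe the children to whom this option applies.

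**Working it through.** **1. The plan's own number.** Section 19.1: about 200 completers × 50% uptake = 100 children; 100 × 50% = 50 per priming group. This reproduces the stated figure of about 100. The protocol gives no expected reaction rate and no expected share of missing diaries, so the values used below for both are assumptions.

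**2. Who enters the reactogenicity set.**
- Section 7.5, item 11: every vaccinated child is observed for at least 15 minutes, and adverse events seen then are recorded. This is safety data.
- Section 18.2: solicited reactions are recorded by the parent on the diary card, from the day of vaccination to day 4.
- Section 7.6, item 1: the diary is reviewed at visit 2.

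A child lost before visit 2, or whose diary is not returned, therefore has safety data but no diary data, and still meets the definition.

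**3. Effect of a literal denominator.** Let r be the true rate and m the share of the set without diary data, with missing diaries unrelated to reactions and children without a diary contributing no event. The reported rate is r × (1 − m), and the shortfall is r × m.

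| Assumed r | m = 0 | m = 2% | m = 5% | m = 10% | m = 20% |
|---|---|---|---|---|---|
| 30% | 30.0% | 29.4% | 28.5% | 27.0% | 24.0% |
| 40% | 40.0% | 39.2% | 38.0% | 36.0% | 32.0% |
| 50% | 50.0% | 49.0% | 47.5% | 45.0% | 40.0% |

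**4. Overall rate against rates by group.** With equal groups the overall rate is (p1 + p2)/2. For assumed rates of 30% and 50%, this is (15 + 25)/100 = 40%. Exact (Clopper-Pearson) 95% intervals:
- overall, 40/100: 30.3% to 50.3%
- one group at 15/50: 17.9% to 44.6%
- the other at 25/50: 35.5% to 64.5%

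The overall figure is 10 points from each group. If both groups were at 30%, the overall rate would also be 30% and the only effect of a split would be on precision: 21.2% to 40.0% with n = 100, against 17.9% to 44.6% with n = 50.

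**5. What a comparison could show.** Power for 50% against 30% with 50 per group, two-sided 5%, normal approximation: Φ((0.20 − 1.96 × √(2 × 0.4 × 0.6/50)) / √((0.25 + 0.21)/50)) = Φ((0.200 − 0.192)/0.0959) = Φ(0.083), or about 53%. A split would therefore be mainly descriptive.

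**The case against.** A reader might infer that the protocol plans to pool the two priming groups and that its reaction rates will be understated. The document supports neither inference. No section says that the groups will be combined. The Chi-square or Fisher rule in Section 19.2 is not limited to antibody endpoints, and comparisons are to follow the allocated groups. No section says that a missing diary counts as no reaction, and an analysis population is not automatically the denominator of every item within it. Section 19.2 promises a full statistical analysis plan, where table layout and item-level denominators are commonly settled.

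It would also go too far to say that every immunogenicity objective is comparative. The primary objective concerns PCV13-primed children alone, and the B cell objective is to measure. A descriptive aim for reactogenicity is a legitimate choice. Section 4 mentions a gap in immunogenicity data for the booster option, not a gap in reactogenicity data.

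These points stand, and they make the concern conditional. They do not remove it. The population definition is stated text, so a statistical analysis plan with a diary-based denominator would depart from the only base the protocol gives. The general rule in Section 19.2 does not settle the split, because the reactogenicity text in Section 19.4 is confined to description and names no group. The per-protocol analysis is not a sure safeguard: Section 19.4 refers to points 2 a, b or c of Section 8.2, but numbered point 2 there has only a and b. If the unnumbered list below it is meant, exclusion for non-compliance is discretionary.

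**Conclusion.** The point holds in conditional form. The reactogenicity population is too loose to be the denominator for diary-based reactions. Used literally, it lowers each solicited rate by r × m: 4 points at an assumed 40% with 10% of diaries missing, 8 points with 20% missing, and nothing if diaries are complete. The direction is certain under that reading; the size is not, because the protocol gives neither input.

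On priming group, the protocol leaves unspecified what its antibody items specify. An overall rate alone would lie 10 points from each group at assumed rates of 30% and 50%, and would do no harm if the groups were equal.

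The endpoint is secondary and descriptive, and nothing here touches the primary analysis. The change is worth making because it is nearly free.

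**What to change.** In Section 19.4:

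- For each solicited reaction, define the denominator as vaccinated children with at least one diary entry for that reaction in days 0 to 4, and report how many vaccinated children have none.
- Keep the broad set for serious adverse events and unsolicited events.
- Present each solicited rate by allocated priming group as well as overall, with exact 95% confidence intervals, and give the between-group difference with a 95% confidence interval, labelled descriptive.

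No new data are needed; only the text and the table layout change. The costs are wider intervals per group (about 50 children instead of 100) and possibly slightly higher reported rates. A diary-based denominator removes the dilution, but it would not correct for diaries that are missing for reasons related to the reactions themselves, which is why the number missing should be shown.
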